#### Secondary endpoints

The secondary endpoints of this study included 3-year OS, 3-year LRFS, 3-year DMFS, and QoL.

Three-year OS is defined as the percentage of patients in this study who are still alive at 3 years measured from the date of randomization. In this study, locoregional recurrence was defined as recurrence at the anastomotic site, tumor bed, remnant stomach, or regional lymph nodes site, and distant metastasis is defined as non-regional lymph node recurrence, peritoneal seeding, and metastasis to other organs. Three-year LRFS and DMFS are defined as the percentage of patients who are without locoregional recurrence or distant metastasis at 3 years measured from the date of randomization respectively. EORTC QLQ-C30 and QLQ-STO22 questionnaires will be used to evaluate QoL of patients at baseline, every 4 weeks during treatment and every visit after treatment.

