### Study design

This is a prospective, randomized controlled trial to evaluate the efficacy of adjuvant radiotherapy for locally advanced EGJ adenocarcinoma after D2 resection. The trial was conducted at the Cancer Hospital of the University of Chinese Academy of Sciences (Zhejiang Cancer Hospital). We anticipated that adjuvant radiotherapy can improve the 3-year DFS by 10%, thus providing strong evidence for adjuvant therapy for locally advanced EGJ adenocarcinoma. Our study has been registered at http://clinicaltrials.gov (ID: NCT03973008).

After providing the signed informed consent, eligible subjects will be randomly assigned to receive adjuvant chemotherapy plus chemoradiotherapy (experimental group) or adjuvant chemotherapy alone (control group) in a ratio of 1:1. Randomization will be stratified by whether the EGJ is invaded or not and by postoperative stage. Patients in adjuvant chemotherapy group (control group) will receive eight cycles of SOX regimen chemotherapy; while patients in adjuvant chemotherapy plus chemoradiotherapy group (experimental group) received two cycles of SOX, then concurrent chemoradiotherapy (45 Gy of radiation with S-1 concurrent oral chemotherapy), followed by four additional cycles of SOX. All adjuvant therapy should begin within 4–6 weeks after surgery. Patients enrolled in this study should complete 3-year follow-up after randomization. The date and location of the first recurrence, as well as the date of death, will be documented. The study flow chart is shown in Fig. 1, and the schedule of enrollment, interventions, and assessments is shown in Fig. 2. The Standard Protocol Items: Recommendations for Interventional Trials (SPIRIT) checklist is provided in Additional file 1.

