#### Exit criteria

Cannot be treated according to the scheme of the study.Grade 4 allergic reactions or severe adverse reactions to research drug.Disease progression in the course of the study.Pregnant and/or not using adequate contraceptive measures.Researchers judged that subjects should not continue the study.Subjects request withdrawal.

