### Concurrent chemoradiotherapy regime

Technique of irradiation: intensity-modulated radiation therapyPreparation prior to CT simulation: fast 4 h and drink 100 ml of water (including 5 ml of contrast agent) 30 min prior to scan; patients with remnant stomach drink additional semiliquid diet (like congee) 10 min before scanningTechnique of simulation: patients in the supine position with forearm on forehead, and use custom immobilization device (e.g., thermoplastic mask) to fix body from lower thorax to lower abdomen. The scanning range is from the apex of lung to the pelvic inlet, with 5-mm slice thickness. Intravenous contrast should be used whenever available unless allergic to contrast, old age, or with serious complications.Irradiation field: the clinical target volume (CTV) include anastomosis with a 3-cm margin in the cranio-caudal direction, and regional lymph node drainage area [No.110 (below carina), 20, 1-3, 7-9, 11 (proximal 1/3), 16a1-2]. The planning target volume (PTV) will be obtained by expanding the CTV by 5–7mm in radial direction, and by 10mm in cranio-caudal direction.Dose prescription and fractionation: a total dose of 45 Gy at 1.8 Gy per day, 5 days per week, for 5 weeks. Dose prescription and recording should comply with the recommendations of the ICRU 83.Organ at risk (OAR) volume definition and dose constraints: the complete volumes of the remnant stomach, the liver, the kidneys, the lungs, and the heart have to be delineated. Intestine and spinal cord must be outlined the volume between above and below 2cm range of PTV. In this study, the normal tissue dose constraints are shown in Table 2.Concurrent chemotherapy: S-1 given orally twice a day (half an hour after breakfast and dinner), Monday to Friday, during radiotherapy, and the dose of S-1 is shown in Table 1.

**Table 2 Tab2:** Normal tissue dose constraints

Organs	Dose constraints
Remnant stomach	V40 < 50% (no hot spot)
Liver	V30 < 40%
	Dmean < 18Gy
Kidney	V20 < 30%
Lung	V20 < 20%
Heart	V30 < 30%
Intestine	Dmax ≤ 50Gy
Spinal cord	Dmax < 40 Gy

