### Follow-up

Patients should be followed up once every 3 months within 2 years after operation and once every 6 months 2 years after operation until 5 years. Follow-up contents include physical examination, performance status monitoring, weight monitoring, routine blood test, blood chemistry, tumor markers (including CEA and CA19-9), adverse events, and QoL assessment. Chest, abdominal, and pelvic CT should be performed every 6 months, and gastroscopy is recommended once a year. If new symptoms or symptoms worsen, patients should receive follow-up visit at any time. The recurrence and/or metastasis must have biopsy or clinical imaging evidence, and the time and location of recurrence and/or metastasis should be recorded in detail.

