### Statistical analysis

In this study, the sample size was estimated by statisticians. The 3-year DFS of the experimental group is expected to be increased from 47 to 60% (δ=0.13), which provides strong evidence for adjuvant treatment of locally advanced EGJ adenocarcinoma. With a one-sided alpha =0.05 and 1 − *β*=0.8, 172 per group would be necessary, and 206 endpoint events need to be observed. Given an estimated dropout rate of 10%, the required total sample size would be 378. Patients enrolled in this study would be randomly divided into experimental group and control group, stratified by whether the EGJ is invaded or not and by postoperative stage. The ratio of the two groups was 1:1.

The analysis was based on the intention-to-treat (ITT) population. The ITT population should include all patients receiving randomization. Per-protocol (PP) population should include all patients who received at least two cycles of chemotherapy and completed radiotherapy for experimental group and received at least four cycles of chemotherapy for control group.

Comparison of baseline data between the two groups: if the quantitative data is normal distribution, *t* test is used; if it is not, rank sum test is used; *χ*^2^ test is used for qualitative data. Survival analysis is carried out by SPSS software package. Log rank *χ*^2^ analysis is used for comparison between the two groups, and Cox regression model is used in multivariate analysis. *χ*^2^ test is used to compare the recurrence rate, metastasis rate, and the incidence of side effects between the two groups. Two-tailed test is used, and *p* < 0.05 is considered statistically significant.

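### Four-weekly quality-of-life assessment is tied to being on treatment, so patients who stop early are assessed about half as often and have no scheduled score at about weeks 12 and 16

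*Protocol article*

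**What the plan says.** QoL is a named secondary endpoint. Under Secondary endpoints, the QLQ-C30 and QLQ-STO22 are to be used to "evaluate QoL of patients at baseline, every 4 weeks during treatment and every visit after treatment".

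The Follow-up section sets the visit interval: "Patients should be followed up once every 3 months within 2 years after operation", then 6-monthly to 5 years. The visit contents include "adverse events, and QoL assessment".

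Under Study design, control patients "will receive eight cycles of SOX regimen chemotherapy". Experimental patients have two SOX cycles, chemoradiotherapy and four more cycles. SOX cycles last 3 weeks. The radiotherapy prescription is "a total dose of 45 Gy at 1.8 Gy per day, 5 days per week, for 5 weeks". Adjuvant therapy starts 4 to 6 weeks after surgery.

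Three other statements bear on the point. The first exit criterion is "Cannot be treated according to the scheme of the study", and severe adverse reactions and disease progression are also listed. Study design says: "Patients enrolled in this study should complete 3-year follow-up after randomization". Statistical analysis says: "The ITT population should include all patients receiving randomization".

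**The concern.** The 4-weekly schedule is defined by treatment status, not by time from randomization. The sections on serious adverse events, dose modification and radiotherapy interruption all foresee stopping for toxicity, and only the experimental arm can meet the radiotherapy rules. Sampling of QoL therefore thins out after an event that is related to how the patient feels and that may be unequal between arms.

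QoL is the patient-reported measure against which any gain in disease-free survival from added radiotherapy will be weighed. Radiotherapy occupies about weeks 7 to 11 (two 3-week cycles, then 5 weeks). The weeks just after it are when a cost of chemoradiotherapy might show, and that is where early stoppers have no scheduled questionnaire.

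**Working it through.** The article gives no sample size, power or effect size for QoL, so there is no stated figure to reproduce. The check is a count of scheduled assessments from the article's own intervals. Weeks run from the start of treatment, with baseline at that start and no gaps between courses.

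**Planned treatment length**
- Control: 8 × 3 = 24 weeks, so 4-weekly assessments at weeks 4, 8, 12, 16, 20 and 24: 6.
- Experimental: 2 × 3 + 5 + 4 × 3 = 23 weeks, so assessments at weeks 4, 8, 12, 16 and 20: 5.

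**Operation-timed visits**
- Taking 3 months as 13 weeks, the first two visits fall 13 and 26 weeks after surgery.
- With treatment starting 4 weeks after surgery: 13 − 4 = week 9 and 26 − 4 = week 22.
- With treatment starting 6 weeks after surgery: 13 − 6 = week 7 and 26 − 6 = week 20.

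**Post-baseline assessments to week 24, literal reading**

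| Stops at week | On-treatment weeks | Later visits (4-week / 6-week start) | Total |
|---|---|---|---|
| 6 | 4 | 9, 22 / 7, 20 | 3 |
| 9 or 11 | 4, 8 | 22 / 20 | 3 |
| 12 | 4, 8, 12 | 22 / 20 | 4 |
| 16 | 4, 8, 12, 16 | 22 / 20 | 5 |
| Completer, experimental | 4 to 20 | none by week 24 | 5 |
| Completer, control | 4 to 24 | none by week 24 | 6 |

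Stopping at week 7 or 8 gives 2 to 4, depending on which side of the stop the first visit falls. Hence about 3 for weeks 6 to 11. Against a completer this is 3/6 = 50% (control) or 3/5 = 60% (experimental).

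**The gap.** A patient who stops at week 9, 10 or 11 was last assessed on treatment at week 8 and is next assessed at week 20 to 22, so the interval is 20 − 8 = 12 to 22 − 8 = 14 weeks. Weeks 12 and 16 fall inside it.

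**Sensitivity to reading.** If the 3-monthly visits also run during treatment, a control completer has 6 + 2 = 8, an experimental completer 5 + 2 = 7, and a patient stopping at week 10 has 2 + 2 = 4. Weeks 12 and 16 remain empty for the early stopper.

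**What this could do to a mean (assumptions only).** Suppose an analysis used only the 4-weekly scores and discarded early stoppers' visit scores. With stopping shares pE and pC and a lasting decrement d, the arm difference would shift by (pE − pC) × d. For d = 15 points, 20% against 10% stopping gives 0.10 × 15 = 1.5 points, and 30% against 10% gives 0.20 × 15 = 3.0. Equal stopping gives 0, and more stopping in the control arm reverses the sign. None of these inputs is in the article.

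**The case against.** A reader might infer that the whole QoL comparison is conditioned on tolerating treatment. The article does not support that. The same sentence continues assessment after treatment, the Follow-up section includes QoL at each visit, and the intention-to-treat population is everyone randomized.

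A reader might also infer a spurious advantage of 1.5 to 3 points for the experimental arm. That needs assumed stopping rates, a decrement that persists after treatment ends, and an analysis that discards off-grid scores. The article states no such analysis, and the QoL method may be in an analysis plan that is not shown. Scores may recover after stopping. The experimental arm has radiotherapy but six SOX cycles against eight, so the direction of unequal stopping is not established either.

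The literal reading is itself open to challenge. The phrase on treatment could mean the planned treatment period, and the schedule figure (Fig. 2) is not available to settle it. A grade 4 reaction can end chemotherapy while radiotherapy later resumes, so it need not end the 4-weekly schedule. Withdrawals are recorded in the case report form, and a longitudinal model using actual assessment times could use every score collected.

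These objections remove the stronger claims but not the point. The intention-to-treat rule fixes who is analysed; it does not create questionnaires that were never scheduled. A model can bridge weeks 12 and 16 for early stoppers, but only on assumptions that the data cannot test. If the planned period was meant, one sentence would say so.

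**Conclusion.** The point holds as a weakness in a stated data-collection rule. On the literal reading, a patient who stops at about weeks 6 to 11 has about 3 post-baseline QoL assessments by week 24, against 5 or 6 for a completer, and none scheduled at about weeks 12 and 16. At those times the scheduled scores come essentially only from patients still on treatment. The counts rest on a 13-week quarter, treatment without gaps, and a start 4 to 6 weeks after surgery.

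No size or direction of bias can be given. Both depend on stopping rates by arm, recovery after stopping and the analysis, none of which the article provides.

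The exit criteria could make the loss larger. The article does not say whether a patient who meets one leaves treatment only or the study as well. If it means the study, QoL would stop altogether, which conflicts with the 3-year follow-up required of enrolled patients.

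This is a worthwhile, inexpensive improvement to a secondary endpoint. It does not affect the primary analysis.

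**What to change.** Define the QoL schedule by time from randomization, identically in both arms: baseline, every 4 weeks to week 24 whether or not study treatment continues, then at the follow-up visits. Allow completion by telephone or post for patients off treatment. Every patient then has 6 scheduled post-baseline assessments to week 24.

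State that meeting an exit criterion does not end QoL collection unless the patient withdraws consent to it, so that the exit criteria agree with the 3-year follow-up under Study design.

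The cost is up to about four extra questionnaires per early stopper (weeks 12, 16, 20 and 24 for a patient stopping at week 8), with no added clinic visit if done remotely. The downside is a small burden on patients who have already stopped. No treatment rule changes. Recruitment was expected to run to 30 June 2022, so an amendment could help only patients not yet past week 24 when it takes effect; missed assessments cannot be recovered.

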### Safety reporting

#### Adverse events

Adverse events are defined as any adverse medical event that occurs between the inclusion in the study with the signing of the informed consent and the last visit, regardless of whether there is a causal relationship with the drugs or treatments being studied.

Adverse events include the following:
All suspected adverse drug reactions (ADR)All reactions due to drug overdose, abuse, withdrawal, allergy, or toxicityObviously unrelated diseases, including the aggravation of pre-existing diseasesInjury or accidentAbnormalities found by physiological or physical examinations and requiring clinical treatment or further examination (unlike repeated validation examinations); abnormalities found in laboratory tests require clinical treatment or further investigation (unlike repeated validation tests); if these abnormalities are related to another reported event (e.g., elevated liver enzymes in jaundice patients), they should be described in the notes to the clinical event report and not listed as a separate adverse event.

#### Adverse event record

Research physicians should use concise medical terminology to report all adverse events directly observed by physicians or spontaneously reported by subjects. In addition, patients should be asked about adverse events every time they visit a doctor at the beginning of treatment, fill in the adverse event record table truthfully, and record the occurrence time, severity, duration, measures taken and outcome of adverse events. Adverse events should be recorded in the adverse events table of case report form (CRF).

#### Grading of adverse events

Adverse events were classified into grades 1–4 according to the National Cancer Institute Common Terminology Criteria for Adverse Events version 4.0 (NCI-CTCAE v4.0) and the European Organization for Research and Treatment of Cancer (EORTC)/Radiation Therapy Oncology Group (RTOG) score:
Grade 1: Mild, asymptomatic, or mild symptoms, only clinical diagnosis or symptoms, can be toleratedGrade 2: Medium, has a certain impact on normal lifeGrade 3: Severe, unable to carry out normal daily activities; leading to hospitalization or prolonged hospitalizationGrade 4: Life threatening, if emergency intervention is needed; otherwise, there is a direct risk of deathGrade 5: Death

#### Serious adverse events

When an adverse event meets one or more of the following criteria, it is classified as a serious adverse event (SAE):
Causing deathLife-threateningNeed for hospitalization or extended hospitalizationCausing persistent or severe disability or dysfunctionCongenital deformity or birth defectMajor medical events

Any serious adverse events in the course of clinical research must be reported by fax or telephone to the ethics committee and the principal investigator within 24 h. The principal investigator will collect data and reports according to SFDA and Ministry of Health’s reporting requirements on adverse reactions. Researchers must fill in a serious adverse event form to record the occurrence time, severity, duration, measures taken, and outcome of serious adverse events.

Once SAE occurs, all antineoplastic therapy should be discontinued immediately, and the relationship between adverse events and research drugs or radiotherapy should be assessed, and appropriate symptomatic and supportive treatment should be given until the patient recovers or remains stable.

### Dose modification

According to CTCAE v4.0, the toxicities during the study should be graded. When adverse drug reactions occur, the dose of drugs should be reduced according to the following principles, or even discontinue treatment. Details of each patient’s dose reduction and withdrawal should be recorded in the CRF table.

#### Dose reduction/withdrawal principle for adverse drug reactions of concurrent chemotherapy and adjuvant chemotherapy

No special treatment should be given when grade 1 adverse reactions occurS-1/oxaliplatin should be discontinued and given symptomatic treatment when grade 4 leucopenia, grade 3 gastrointestinal adverse reactions, grade 2 anemia and thrombocytopenia, and grade 2 liver and kidney dysfunction occur. If the grade of adverse reactions dropped to 0–1 within 5 days after treatment, the initial dose of S-1/oxaliplatin was restored; if not, consideration should be given to reducing dose of S-1/oxaliplatin to 80% of the initial dose. If the above adverse reactions persist for more than 3 days after symptomatic treatment and dose reduction, or other adverse reactions with new grade 2 or higher occur again, S-1/oxaliplatin should be terminated.When other grade 3 adverse reactions occur, the treatment principle is the same as that of corresponding grade 2 adverse reactionsIf any grade 4 adverse reactions occur, the concurrent chemotherapy or adjuvant chemotherapy should be stopped and not continued.

#### Principles of interruption or discontinuation of radiotherapy

When the acute grade 3 radiation toxicities occurs, radiotherapy should not be interrupted and symptomatic treatment should be given. If it does not recover to grade 0–1 within 7 days, radiotherapy should be interrupted and restarted after the grade of toxicity return to 0–1. If the same toxicities of above grade 2 reoccur, radiotherapy should be terminated. When radiotherapy is terminated, S-1 should be terminated at the same time.If any grade 4 adverse reactions except leukopenia occurred, radiotherapy should be discontinued. When the adverse reactions recover to grade 0–1, restart radiotherapy, but not chemotherapy.Dose of radiation should not be adjusted unless new adverse reactions occur or the original adverse reactions are aggravated.

### Follow-up

Patients should be followed up once every 3 months within 2 years after operation and once every 6 months 2 years after operation until 5 years. Follow-up contents include physical examination, performance status monitoring, weight monitoring, routine blood test, blood chemistry, tumor markers (including CEA and CA19-9), adverse events, and QoL assessment. Chest, abdominal, and pelvic CT should be performed every 6 months, and gastroscopy is recommended once a year. If new symptoms or symptoms worsen, patients should receive follow-up visit at any time. The recurrence and/or metastasis must have biopsy or clinical imaging evidence, and the time and location of recurrence and/or metastasis should be recorded in detail.

### Ancillary and post-trial care

Only when treatment-related complications occur, the corresponding ancillary care is permitted. There is no prearranged post-trial care.

### Statistical analysis

In this study, the sample size was estimated by statisticians. The 3-year DFS of the experimental group is expected to be increased from 47 to 60% (δ=0.13), which provides strong evidence for adjuvant treatment of locally advanced EGJ adenocarcinoma. With a one-sided alpha =0.05 and 1 − *β*=0.8, 172 per group would be necessary, and 206 endpoint events need to be observed. Given an estimated dropout rate of 10%, the required total sample size would be 378. Patients enrolled in this study would be randomly divided into experimental group and control group, stratified by whether the EGJ is invaded or not and by postoperative stage. The ratio of the two groups was 1:1.

The analysis was based on the intention-to-treat (ITT) population. The ITT population should include all patients receiving randomization. Per-protocol (PP) population should include all patients who received at least two cycles of chemotherapy and completed radiotherapy for experimental group and received at least four cycles of chemotherapy for control group.

Comparison of baseline data between the two groups: if the quantitative data is normal distribution, *t* test is used; if it is not, rank sum test is used; *χ*^2^ test is used for qualitative data. Survival analysis is carried out by SPSS software package. Log rank *χ*^2^ analysis is used for comparison between the two groups, and Cox regression model is used in multivariate analysis. *χ*^2^ test is used to compare the recurrence rate, metastasis rate, and the incidence of side effects between the two groups. Two-tailed test is used, and *p* < 0.05 is considered statistically significant.

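### The sample size is labelled one-sided alpha 0.05, but 206 events with 172 per group is the two-sided 0.05 design, and the analysis rule is two-tailed

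*Protocol article*

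**What the plan says.** All the key statements stand in the Statistical analysis section of the protocol article.

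- Effect: "The 3-year DFS of the experimental group is expected to be increased from 47 to 60" per cent, a difference of 13 points.
- Error rates: "With a one-sided alpha =0.05", with power 0.8.
- Result: "172 per group would be necessary, and 206 endpoint events need to be observed".
- Inflation: "Given an estimated dropout rate of 10%, the required total sample size would be 378".
- Allocation: "The ratio of the two groups was 1:1".
- Test: a log-rank chi-square ("analysis is used for comparison between the two groups, and Cox regression model is used in multivariate analysis").
- Significance rule, at the end of the section: "Two-tailed test is used", with p below 0.05 as significant. The primary comparison is not exempted.

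Two other places bear on timing. Study design says "Patients enrolled in this study should complete 3-year follow-up after randomization". Trial status gives recruitment from 1 July 2019 to an expected close on 30 June 2022, which is 3 years.

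**The concern.** One section gives two different type I error rates for the same primary comparison, and nothing elsewhere in the article reconciles them. If the one-sided 0.05 were the real design, 206 events would be far more than 80% power requires. If the two-tailed rule is the real design, the stated alpha is wrong.

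What is at stake is the success criterion of an open-label phase III superiority trial. With 206 events, the largest observed hazard ratio that reaches significance is exp(−2z/√206):

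- one-sided 0.05 (z = 1.645): 0.795
- two-sided 0.05 (z = 1.960): 0.761

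A result between these values has a two-sided p between 0.05 and 0.10. It would meet the alpha in the design statement and fail the analysis statement. That choice should not be open once results are known.

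**Working it through.** **Inputs from the protocol.** 3-year DFS 47% and 60%; power 0.80; 1:1 allocation; log-rank test; 206 events; 172 per group, so 344 in total (all Statistical analysis). Three years of accrual (Trial status) and 3 years of follow-up per patient (Study design).

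**Assumptions added here.** Proportional hazards, exponential DFS, uniform accrual, analysis 3 years after the last patient enters, and no loss to follow-up in the 344.

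**Step 1. Hazard ratio.** HR = ln 0.60 / ln 0.47 = 0.6766, so ln HR = −0.3907 and (ln HR)² = 0.1527.

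**Step 2. Events.** Schoenfeld's formula for 1:1 allocation is D = 4(z_α + z_β)² / (ln HR)², with z_β = 0.8416.

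- Two-sided 0.05: 4 × (1.960 + 0.8416)² / 0.1527 = 4 × 7.849 / 0.1527 = 205.7, rounded up to 206. This is the protocol's figure.
- One-sided 0.05, as stated: 4 × (1.645 + 0.8416)² / 0.1527 = 4 × 6.183 / 0.1527 = 162.0.

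Other formulas do not rescue the one-sided label. At one-sided 0.05, Freedman gives 167 and Lachin–Foulkes about 165. At two-sided 0.05 they give 211 and 210, within 3% of 206.

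**Step 3. Power with 206 events.** Power = Φ(√206/2 × 0.3907 − z_α).

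- One-sided 0.05: 87.7%
- Two-sided 0.05: 80.1%

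The stated 80% fits only the two-sided reading.

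**Step 4. Patients.** The yearly hazards are −ln 0.47/3 = 0.2517 and −ln 0.60/3 = 0.1703. With 3 years' uniform accrual and 3 further years of follow-up, the probability of an event is 1 − (e^(−3λ) − e^(−6λ))/(3λ).

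- Control: 1 − (0.470 − 0.2209)/0.7550 = 0.670
- Experimental: 1 − (0.600 − 0.360)/0.5108 = 0.530
- Mean: 0.600

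Expected events from 344 patients are 344 × 0.600 = 206.4. Conversely, 205.7/0.600 = 343 patients, or 172 per group. The one-sided design on the same timeline needs 162/0.600 = 270, or 135 per group.

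**Step 5. Rival routes to 172 at one-sided 0.05.**

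| Route | Per group | Events |
|---|---|---|
| Two proportions, unpooled variance | 179 | none computed |
| Two proportions, pooled variance | 181 | none computed |
| Two proportions, continuity-corrected | 197 | none computed |
| Log-rank, every patient followed exactly 3 years (162/0.465) | 174 | 162 |
| **Protocol** | **172** | **206** |

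At 172 per group, the two-proportion test has 78.6% power (unpooled) or 78.2% (pooled). The fixed 3-year log-rank route comes close to 172, but it needs 162 events, and 344 patients would supply only 344 × 0.465 = 160. None of these routes produces the pair.

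**The case against.** **172 alone does not settle the matter.** The primary endpoint is a 3-year percentage. If events are counted only within 3 years of randomization, 344 patients give 160 events, and at one-sided 0.05 that is 79.6% power. One could argue that the one-sided label and 172 belong together and that 206 is the slip. This stands as a caveat about 172 taken alone. It does not explain 206, whereas the two-sided reading yields both numbers.

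**The match to 172 rests on timing that the sample-size paragraph does not state.** This is true. With 3 years' accrual and only 2 years' follow-up, 344 patients yield about 175 events; with 5 years' follow-up, about 252. The 3 + 3 timing is inferred from other sections. The mismatch between 206 events and one-sided 0.05 does not depend on timing at all.

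**The only sentence that says when a result is significant is the two-tailed one.** On that reading the one-sided alpha is just a planning input, and no false-positive inflation arises unless the written rule is ignored. This largely stands and limits the harm. It does not make the stated planning alpha correct, and it leaves a published one-sided 0.05 that could later be cited in support of a borderline result.

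**The effect size is itself in doubt.** Study design anticipates a 10% improvement rather than 13%; at 47% versus 57%, 206 events give about 56% power two-sided. That conflict needs settling, but it is a separate matter and does not alter which alpha the printed figures were computed from.

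**Conclusion.** The concern holds. For 47% versus 60% at 80% power, the stated one-sided alpha of 0.05 calls for about 162 events (up to 167 by the other formulas), not 206. The printed figure is about 27% above the Schoenfeld requirement (206/162 = 1.27). The pair of 206 events and 172 per group is reproduced exactly at two-sided 0.05, using the recruitment and follow-up periods in the article.

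The event calculation assumes proportional hazards. The patient calculation also assumes exponential DFS, uniform accrual and a 3 + 3 year timeline. That the label, rather than the event count, is wrong is an inference, but a strong one.

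The trial is not underpowered by this error: power is 80.1% under the two-tailed rule. What is wrong is the stated error rate for the primary claim, which leaves a second, laxer threshold in the text. If that threshold were used, the false-positive rate for superiority would be 5% instead of 2.5%.

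**What to change.** In Statistical analysis:

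1. Replace the one-sided alpha of 0.05 with a two-sided alpha of 0.05 (equivalently one-sided 0.025).
2. State the basis of the figures: log-rank test, HR 0.677 derived from 47% versus 60%, 80% power, 206 events, uniform accrual over 3 years and 3 further years of follow-up.
3. Say that two-tailed p < 0.05 is the sole criterion for the primary comparison.

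Before publishing the correction, the trial statistician should confirm the sidedness against the original sample-size calculation. The change should be made and dated before any comparative DFS data are seen.

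The cost is a wording amendment. The 172 per group, the 206 events and the total of 378 are unchanged by it.
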